### Sample size determination

In our preliminary study [16], the mean VAS score before the first *Anma* massage session in cancer survivors was 40.4, which was reduced to 19.6 before the last (eighth) *Anma* massage session. The mean VAS score difference during 2 months was −20.8 (standard deviation (SD) 19.6). We assume for the no *Anma* massage group that the mean difference will be unchanged (that is, zero) and that its SD will be the same as that of the *Anma* massage group (that is, 19.6). To test these differences between the two groups, with a 5% type I error rate and 90% power, a sample size of 14 patients per group is required. For sensitivity analysis, we also consider the following situations: the mean VAS score differences in the no–*Anma* massage group will be −5, –7.5 and −10, in which case sample sizes of 24, 33 and 49 patients per group, respectively, are required for 90% power, and 18, 25 and 37 patients per group, respectively, are required for 80% power. Therefore, the planned sample size will be 30 participants per group (60 participants in total). A sample size of 30 patients per group will also account for possible data loss or dropouts.

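### None of the seven stated sample sizes follows from the stated SD of 19.6; all are about 30% too small, so the power implied for 30 per group is overstated

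*Protocol article*

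**What the plan says.** Everything here is in the protocol article, Sample size determination, unless noted.

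- Anma group, from the preliminary study: "The mean VAS score difference during 2 months was −20.8 (standard deviation (SD) 19.6").
- Control group, base case: "We assume for the no *Anma* massage group that the mean difference will be unchanged (that is, zero"), and "its SD will be the same as that of the *Anma* massage group (that is, 19.6").
- Base-case result: "with a 5% type I error rate and 90% power, a sample size of 14 patients per group is required".
- Sensitivity scenarios: "the mean VAS score differences in the no–*Anma* massage group will be −5, –7.5 and −10", for which "sample sizes of 24, 33 and 49 patients per group, respectively, are required for 90% power". For 80% power the section gives 18, 25 and 37 per group.
- The planned 30 per group is presented as following from these figures, and the section adds: "A sample size of 30 patients per group will also account for possible data loss or dropouts". It gives no dropout rate.

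The Statistical analysis section makes all reported P values two-sided and sets the significance level at 0.05. Its primary analysis is an analysis of covariance of the change in VAS, adjusted for baseline VAS and age. A two-sample t-test of the changes is an additional analysis. The sample size section mentions no correlation, residual SD or other variance reduction.

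**The concern.** The section gives every input that a two-sample comparison of mean changes needs, so its results can be checked directly. A difference of 20.8 against an SD of 19.6 is a standardised effect of 20.8/19.6 = 1.06, and 14 per group is too few for 90% power at that effect size.

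The figures matter because the choice of 30 per group rests on them. Read against the stated sizes, 30 exceeds the 24 needed for 90% power at a control change of −5 and the 25 needed for 80% at −7.5, and leaves a margin for losses in both. These scenarios are realistic: controls have a 40-minute relaxing chat with a massage therapist, so some improvement in that arm is possible. The Discussion calls the trial confirmatory and expects its result, positive or negative, to be reflected in guidelines. If the sizes are wrong, a null result would be read as better powered than it was.

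**Working it through.** **Inputs.** SD of change 19.6 in both groups; two-sided α = 0.05; equal allocation. Differences between groups: 20.8 − 0 = 20.8; 20.8 − 5 = 15.8; 20.8 − 7.5 = 13.3; 20.8 − 10 = 10.8.

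**Formulas.** Normal approximation: n per group = 2(z₀.₉₇₅ + z_power)² × SD² / d². Exact: the smallest n at which the two-sample t-test reaches the target power, using the noncentral t distribution with 2n − 2 degrees of freedom and noncentrality (d/SD)√(n/2).

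**Base case by hand.** 2 × (1.960 + 1.282)² × 19.6² / 20.8² = 18.7, so 19 per group; the exact t-test needs 20. The stated figure is 14.

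**All seven figures, SD 19.6:**

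| Control change | Difference | Target power | Stated n | Normal approx. | Exact t | Power at stated n (exact t) |
|---|---|---|---|---|---|---|
| 0 | 20.8 | 90% | 14 | 19 | 20 | 77.1% |
| −5 | 15.8 | 90% | 24 | 33 | 34 | 78.0% |
| −7.5 | 13.3 | 90% | 33 | 46 | 47 | 77.5% |
| −10 | 10.8 | 90% | 49 | 70 | 71 | 77.0% |
| −5 | 15.8 | 80% | 18 | 25 | 26 | 65.2% |
| −7.5 | 13.3 | 80% | 25 | 35 | 36 | 65.2% |
| −10 | 10.8 | 80% | 37 | 52 | 53 | 64.7% |

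Each stated size is about 70% of the size needed (for example 14/20 = 0.70 and 49/71 = 0.69).

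**Attempts to reproduce the stated figures.**

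- One-sided 5% gives 16, 28, 38 and 58 at 90% and 20, 28 and 42 at 80% (exact t). None matches, and a one-sided test would conflict with the two-sided rule.
- The one-sample formula gives about 9, 16, 23 and 35, then 12, 17 and 26. None matches.
- Inflating for dropout or for a rank test makes the sizes larger, so further from the stated ones.
- Solving for the SD, the two-sided t-test returns all seven stated sizes exactly for an SD from about 16.17 to 16.32. At 16.16 one size becomes 23 instead of 24; at 16.33 one becomes 50 instead of 49.

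The seven figures are therefore consistent with one another, but not with the SD printed beside them. An SD of 16.3 corresponds to a variance 1 − (16.3/19.6)² = 31% below that implied by 19.6.

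**Power of the planned trial, SD 19.6, unadjusted two-sample t-test.** The documents give no dropout rate; 10% is an assumption for illustration (30 × 0.9 = 27 per group).

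| Control change | 30 per group | 27 per group | Level implied by the stated sizes |
|---|---|---|---|
| 0 | 98.1% | 96.9% | at least 90% |
| −5 | 86.7% | 82.8% | at least 90% |
| −7.5 | 73.4% | 68.7% | at least 80% |
| −10 | 55.5% | 51.1% | none (stated 37 and 49 already exceed 30) |

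**The case against.** The arithmetic is not in dispute; the case on the other side concerns consequence.

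*The primary analysis is the analysis of covariance, not the t-test.* Adjustment for baseline VAS and age reduces the residual SD to 19.6 × √(1 − r²), where r is the correlation between the change and the covariates. The documents give no r. Taking values as assumptions, with 30 per group and ignoring the small loss of degrees of freedom, power for control changes of 0, −5, −7.5 and −10 is 98.9/89.6/77.3/59.5% at r = 0.3, 99.3/91.8/80.5/62.9% at r = 0.4 and 99.7/94.3/84.7/67.8% at r = 0.5. From r of about 0.4 both implied levels would be met before dropout, and r of about 0.56 would account for the stated sizes. This stands as a limit on the harm. It does not repair the section, which attributes its sizes to an SD of 19.6 and claims no reduction.

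*The printed SD may be the error.* The figure 19.6 is also the pilot's mean VAS before the eighth session (40.4 − 20.8 = 19.6), so it may have been copied into the wrong place. If the true SD of change was about 16.3, the sizes are right and no power is overstated. The protocol alone cannot settle this.

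*The effect is confined.* The article prints no power for 30 per group; it is implied by comparing 30 with 24 and 25. The base case is safe, 80% power is still met at −5 (26 needed), and at −10 the article's own sizes already exceed 30. All of this is correct. Two of the sensitivity rows lose the margin that the text implies.

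**Conclusion.** The concern holds. With the stated SD of 19.6 and a two-sided 5% two-sample test, all seven sample sizes are wrong by about 30%: 20 instead of 14; 34/47/71 instead of 24/33/49; 26/36/53 instead of 18/25/37. At the stated sizes, power is 77–78% where 90% is claimed and about 65% where 80% is claimed.

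For the planned 30 per group, the implied 90% at a control change of −5 is 86.7%, and the implied 80% at −7.5 is 73.4%, both before dropout. The dropout allowance is real only for a control change of 0, where 20 analysed per group suffice for 90%, and for −5 at 80% power, where 26 suffice.

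These power figures assume the SD really is 19.6 and take no credit for covariate adjustment. If either assumption is wrong, the overstatement shrinks or disappears, but the section still misstates the input behind its figures. It must be corrected in any case.

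**What to change.** Go back to the preliminary study's individual data and confirm the SD of the change in VAS. Then make one of these corrections in Sample size determination:

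1. **If the SD is 19.6 and no adjustment was assumed:** replace the sizes with 20 (base case), 34/47/71 (90%) and 26/36/53 (80%). State that 30 per group gives about 98.1%, 86.7%, 73.4% and 55.5% power for control changes of 0, −5, −7.5 and −10 before dropout, by the unadjusted t-test. Limit the dropout statement to a control change of 0 and, at 80% power, −5.
2. **If the SD was about 16.3:** correct the printed SD and keep the sizes.
3. **If a covariate adjustment was built in:** state the assumed correlation or residual SD (a variance reduction of about 31% would fit) and its source.

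The cost is a wording correction to one section. The enrolment target, design and analysis stay as they are. Under the first option, the stated power becomes less favourable, and a null result should be interpreted against the corrected figures.

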### Statistical analysis

Analysis of pretreatment characteristics and efficacy analysis will be performed according to the modified intention-to-treat principle and will include all participants who receive at least one *Anma* massage session in the *Anma* massage therapy group and one relaxing chat in the no–*Anma* massage group. If necessary, we might also perform sensitivity analyses, adding all eligible patients who are introduced by medical doctors to the coordinating office but are not registered.

The primary end point is VAS score improvement over the 2-month study period. For primary analysis, we will use the analysis of covariance to compare the mean changes in VAS score over the 2 months between the *Anma* massage group and the no–*Anma* massage group, adjusting for the baseline VAS score and age. If we find other significant prognostic factors, we will use them as additional adjusting factors. We will also use a two-sample *t*-test with Satterthwaite’s approximation to compare the mean changes. We will also test the mean changes in VAS score for each group using a paired *t*-test. For these mean VAS score changes and their differences, we will also calculate two-sided 95% confidence intervals (CIs) to evaluate the clinical effects.

For the secondary end points, we will not consider multiplicity issues. In all analyses, categorical variables will be described in terms of frequency and percentage. The distributions of continuous variables will be described using means, SDs, medians, and minimum and maximum values. A two-sample *t*-test or paired *t*-test will be used to detect differences in continuous variables. Pearson’s χ^2^ test with continuity correction will be used to test differences in categorical variables. If these data are found not to be normally distributed, we will use in their place the Wilcoxon signed-rank test or the Mann-Whitney *U* test, respectively. All reported *P* values will be two-sided. All significance levels will be set at 0.05, and reported CIs will be 95%. In principle, we will use the available-case analysis for missing outcomes. SAS statistical software (version 9.3 or later; SAS Institute, Cary, NC, USA) will be used for all analyses.

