### Randomization

After finishing registration, the patients are allocated by block randomization by the coordinating office to continuous *Anma* massage therapy or no *Anma* massage therapy, except for a single *Anma* massage therapy intervention at the end of the trial period (Figure 1). Allocation adjustment factors are not set in the trial because of insufficient evidence at present regarding which factors affect the effectiveness of *Anma* massage therapy.

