## Discussion

This trial is considered to correspond to a phase III study because of the preliminary study undertaking and because the randomized confirmatory trial has significance for the primary end point set at 5%, addressing the effects of longer-term intervention. This trial will employ adequate methods to reduce bias, such as randomization, a large subject population and analysis according to the intent-to-treat principle.

Regardless of whether the results of this trial are positive or negative, in the current situation, where benefits conferred to the body and mind by *Anma* massage therapy for cancer survivors are controversial, the findings of this trial will help to provide an answer to this controversy and will be reflected in the guidelines for cancer care. At present, patients decide of their own will whether they receive *Anma* massage therapy. Using the evidence-based findings of this trial, medical professionals should be able to explain the benefits conferred by *Anma* massage to cancer survivors and provide higher-quality information to better inform patients in their decisions about whether to receive such therapy.

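### The primary ANCOVA is left open to covariates found significant later, so the confirmatory model is not fixed and type I error can exceed 5%

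*Protocol article*

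**What the plan says.** All references are to the protocol article.

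- **Statistical analysis, primary model.** "For primary analysis, we will use the analysis of covariance to compare the mean changes in VAS score over the 2 months" between the two groups, "adjusting for the baseline VAS score and age".
- **Statistical analysis, next sentence.** "If we find other significant prognostic factors, we will use them as additional adjusting factors".
- **Statistical analysis, second test of the same change.** "We will also use a two-sample *t*-test with Satterthwaite’s approximation to compare the mean changes". The ANCOVA, not this test, carries the label of primary.
- **Statistical analysis, error rate.** "All reported *P* values will be two-sided" and "All significance levels will be set at 0.05, and reported CIs will be 95" per cent.
- **Discussion, status of the trial.** The article states that "the randomized confirmatory trial has significance for the primary end point set at 5" per cent.

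The sentence on further factors stands directly after the definition of the primary model and before the supplementary tests, so on a plain reading it governs the primary analysis. It does not say which variables are candidates, what test or threshold makes a factor significant, where or when the search is made, or whether treatment arm is hidden during it.

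**The concern.** A confirmatory 5% test needs a model settled before the outcome data can influence it. Here two covariates are fixed, and the rest depend on what turns out to be significant. If the search is made in the trial's own outcome data, the same data both choose the model and test treatment within it, and the final p-value is computed as though no choice had been made.

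The way the screen treats the arm matters:

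- **Arm ignored.** With no treatment effect, the chosen set depends only on outcomes and baseline data, which are independent of the random allocation. The later test of treatment should then keep close to its nominal level.
- **Arm in the screening model.** The chosen set depends on the allocation as well, that protection is lost, and the test can reject too often.

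The sentence permits either. At stake are the stated 5% level and the 95% confidence interval of the primary comparison.

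**Working it through.** **Inputs from the document**
- 30 patients per group, 60 in total (Sample size determination).
- Two-sided test at 0.05; baseline VAS and age always in the model (Statistical analysis).

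**Assumptions, because the document gives no figure**
- K = 5, 10 or 20 independent candidate covariates.
- Together the candidates explain either 0% or 30% of the residual variance in VAS change.
- A candidate enters if its own p-value is below 0.05.

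**Is 20 candidates plausible?** The End points section lists 1 global, 5 functional and 9 symptom scales of the QLQ-C30 (15), 4 urine analytes and 3 saliva analytes: 15 + 4 + 3 = 22, before HADS, POMS and MAC. Data collection compares changes in all end points from the first measurement, so each has a baseline value. Twenty is an upper setting that the listed variables can fill. The real variables will be correlated, which the simulation does not model.

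**Chance that at least one irrelevant candidate enters**, 1 − 0.95^K:
- K = 5: 1 − 0.774 = 23%
- K = 10: 1 − 0.599 = 40%
- K = 20: 1 − 0.358 = 64%

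**Type I error by simulation with no treatment effect.** Each run fits the ANCOVA under three rules and counts treatment p-values below 0.05. The Monte Carlo standard error is √(0.05 × 0.95 / runs).

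| K | Variance explained | Runs | Fixed model | Screen ignores arm | Treatment in screening model | MC SE (points) |
|---|---|---|---|---|---|---|
| 5 | 0% | 12,000 | 5.3% | 5.3% | 5.8% | 0.20 |
| 5 | 30% | 12,000 | 5.1% | 4.9% | 5.1% | 0.20 |
| 10 | 0% | 10,000 | 4.9% | 5.0% | 5.8% | 0.22 |
| 10 | 30% | 10,000 | 5.2% | 5.0% | 6.1% | 0.22 |
| 20 | 0% | 5,000 | 5.4% | 5.3% | 7.1% | 0.31 |
| 20 | 30% | 5,000 | 5.3% | 5.3% | 7.9% | 0.31 |

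**Reading the table**
1. The fixed model reproduces the plan's own 5% within simulation error.
2. A mechanical screen that ignores arm also keeps 5%.
3. With treatment in the screening model the rate rises with the number of candidates. Repeat simulations with 10 or 20 candidates gave 5.8 to 8.5%, so the working range over all settings is roughly 5 to 8.5%.
4. When treatment is in the screening model, a constant treatment effect does not alter which covariates are chosen. Coverage of the 95% interval therefore falls by the same amount: at the upper end, 100 − 8.5 = 91.5%.

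**The case against.** The strongest reply is that nothing in the text makes inflation inevitable. A prognostic factor can be sought without reference to treatment, and the table shows that a screen run that way costs nothing in type I error. This stands: the supportable claim is that the rate can exceed 5%, not that it does.

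Three stronger readings might be inferred, and the document does not support them:

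- **The analyst may pick the most favourable model.** The sentence says such factors will be used, which is mandatory, and the ANCOVA is the named primary analysis. Higher error rates that assume a choice among p-values describe a rule the plan does not contain, so none is used here.
- **The search is made in unblinded data.** The article gives neither the source nor the timing of the search. Searching the trial data is the more natural meaning, but evidence arriving from outside is not excluded. What can be said is that no safeguard is stated.
- **The Randomization section admits that prognostic factors are unknown.** It says "Allocation adjustment factors are not set in the trial because of insufficient evidence at present regarding which factors affect the effectiveness of" the therapy. That explains why allocation is not stratified and speaks of factors that alter the treatment's effect, not of prognostic covariates for the ANCOVA. It supplies no candidate list, but it is not evidence for this point.

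Two mitigations deserve credit. The Satterthwaite t-test gives a comparison with no covariate selection, although it is not the primary analysis. An analysis plan that is not shown might also fix a list and a threshold. That would help, but the point here is a rule the article states, not a detail it leaves out: as worded, the primary model follows from what is found significant.

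**Conclusion.** The concern holds in this form: the stated rule leaves the primary model, p-value and confidence interval of a trial described as confirmatory at 5% unfixed in advance, and it can raise type I error. The size is modest and conditional: about 5% if the screen ignores treatment arm, roughly 5 to 8.5% if treatment is in the screening model. These figures assume 30 per arm, 5 to 20 independent candidates and entry at p<0.05; only the group size comes from the document. The defect in specification is clear from the text. The magnitude is illustrative, since the screening procedure is not described. This should be corrected.

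**What to change.** Delete the sentence on additional prognostic factors from the primary analysis, and state the primary ANCOVA as treatment, baseline VAS and age only. If the sponsor wants more covariates in the primary model, name them before any outcome data are seen. Report models with further covariates as supportive, and state that they cannot replace the primary p-value or confidence interval.

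The cost is one sentence. The change does not affect the sample size and needs no new data. The article gives the trial's status as recruiting, so the change could be made before the final analysis. The price is a possible small gain in precision in the primary model from a prognostic factor nobody foresaw; that gain can still be shown in a supportive model.

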### Data collection

Data collection is performed on three occasions in the *Anma* massage group: before and after the first *Anma* massage session (measurements A and B) and before the last (eighth) *Anma* massage session (measurement C) (Figure 1). Data collection is conducted on four occasions in the control group: before and after the relaxing chat session (measurements D and E) and before and after the single *Anma* massage session (measurements F and G) at 2 months (Figure 1).

To assess the effects of continuous *Anma* massage sessions, changes in all end points between measurements A and C are compared with those between measurements D and F.

In addition, to confirm immediate changes following a single *Anma* massage session, which is the secondary objective of the trial, changes in VAS score, POMS score, and levels of 8-hydroxydeoxyguanosine, catecholamine (noradrenaline, adrenaline and dopamine), salivary cortisol, chromogranin A, and s-IgA between measurements A and B are compared with those between measurements D and E. Such changes between measurement F and measurement G are also considered as additional evidence to confirm the immediate effects of a single *Anma* massage session.

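### Continuous secondary and immediate-change outcomes get unadjusted t-tests on change although their baselines are available as covariates, and the fallback rank tests are listed in reversed order

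*Protocol article*

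**What the plan says.** All references are to the protocol article.

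- **Quantity compared (Data collection).** For the 2-month effect, "changes in all end points between measurements A and C are compared with those between measurements D and F". For the immediate effect, which is the secondary objective, the A-to-B change is compared with the D-to-E change for VAS, POMS and the urine and saliva markers. The F-to-G change in the control group is supporting evidence.
- **Primary analysis (Statistical analysis).** The 2-month VAS change is compared by ANCOVA, "adjusting for the baseline VAS score and age". A two-sample t-test and within-group paired t-tests on the same outcome are added.
- **Other continuous variables (same section, next paragraph).** "A two-sample *t*-test or paired *t*-test will be used to detect differences in continuous variables". No covariate is named.
- **Fallback.** "If these data are found not to be normally distributed, we will use in their place the Wilcoxon signed-rank test or the Mann-Whitney" U test, with the two lists linked by the word respectively.
- **Also relevant.** "For the secondary end points, we will not consider multiplicity issues", and "In principle, we will use the available-case analysis for missing outcomes". The Randomization section sets no allocation adjustment factors, and 30 patients per group are planned.

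**The concern.** There are two separate problems in one paragraph.

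First, every outcome measured at A and D has a baseline that could enter as a covariate at no cost, yet only the 2-month VAS change is analysed that way. Even the immediate VAS change loses the adjustment that the same scale receives at 2 months. In a trial of 60 without stratification, some chance baseline imbalance is to be expected across so many scales and markers. A change score removes that imbalance only in part. What is at stake is precision and the conditional accuracy of individual results, not the validity of the tests.

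Second, the rank tests are attached to the wrong designs. An analyst who follows the written rule would apply the signed-rank test to two independent arms and the Mann-Whitney test to before-after data.

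**Working it through.** The article states no figure for the secondary-outcome tests, so there is none to reproduce. Its sample-size figures concern the primary VAS change and play no part here.

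**1. Precision of the change score against ANCOVA**

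Inputs: 30 per arm (Sample size determination). The baseline to follow-up correlation r is not given, so I assume 0.3 to 0.9. I also assume the same SD σ at both times.

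- Variance of a change: 2σ²(1-r)
- Residual variance given baseline: σ²(1-r²)
- Ratio: (1-r²) / [2(1-r)] = (1+r)/2
- Patients per arm that a change-score test needs to match ANCOVA with 30: 30 / [(1+r)/2]
- ANCOVA power where the change-score test has 80% (normal approximation, two-sided 5%): Φ(2.80/√ratio - 1.96)

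**2. Effect of a chance baseline difference**

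If the arms differ by d at baseline, the expected difference in change moves by rd - d = -(1-r)d. One standard error of a baseline difference at 30 per arm is σ√(2/30) = 0.26σ, so the shift has size (1-r) × 0.26σ.

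| assumed r | variance ratio | matching n per arm | ANCOVA power (change score 80%) | shift from a one-SE imbalance |
|---|---|---|---|---|
| 0.3 | 0.65 | 46.2 | 93.5% | 0.18σ |
| 0.5 | 0.75 | 40.0 | 89.9% | 0.13σ |
| 0.7 | 0.85 | 35.3 | 86.0% | 0.08σ |
| 0.9 | 0.95 | 31.6 | 82.0% | 0.03σ |

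The formulas ignore the degrees of freedom spent on the covariates, and they take no credit for adjusting for age.

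**3. Order of the rank tests**

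| listed | t-test | replacement listed in the same place | design the replacement needs |
|---|---|---|---|
| first | two-sample | Wilcoxon signed-rank | paired |
| second | paired | Mann-Whitney | independent groups |

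Both rows are mismatched. To see what the literal rule would do, I simulated 4,000 trials with 30 per arm. The arms were paired arbitrarily, and the switch was made when a Shapiro-Wilk test rejected in either arm. That trigger is my assumption, because the article names none.

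- *Independent arms, type I error:* 0.048 to 0.051 under the literal rule.
- *Independent arms, power:* 65% under the literal rule against 87% with Mann-Whitney for lognormal data with a shift of 0.8. For a skewed-difference example it was 68% against 79% with the order corrected.
- *Independent arms, dependence on pairing:* in one simulated data set the signed-rank p-value ran from 0.050 to 0.79 over 2,000 arbitrary pairings; Mann-Whitney gave 0.093. With unequal arms, which available-case analysis can produce, the test cannot be computed.
- *Paired data (3,000 runs, normal):* Mann-Whitney had type I error of 0.8% at r = 0.5 and 0.1% at r = 0.7. With a shift of 0.5 SD at r = 0.5, its power was 43% against 73% for signed-rank.

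**4. The normality switch itself**

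With the tests in the correct order, the switch kept type I error between 0.044 and 0.052 in the same simulations.

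**The case against.** The strongest reply is that an unadjusted t-test on change is a valid analysis of a randomised comparison. These are secondary outcomes without multiplicity control, and the confirmatory analysis is already adjusted. That stands, and it limits the point to efficiency. The gain also rests on an unknown r. Before and after a single 40-minute session r may well be higher than over 2 months, so the figure of 40 against 30 patients per arm should not be applied to every outcome.

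On the rank tests, the authors use the two-sample and paired t-tests correctly for the VAS in the preceding paragraph. The reversal therefore looks like a slip, and no analyst is likely to pair unrelated patients. That is fair; the simulated losses show what the literal text would do, not what is likely to happen. The sentence still needs correcting.

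A reader might infer four stronger things that the article does not support:

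- *That the baselines go unused.* They are used, by subtraction, because changes are compared.
- *That imbalance passes undiminished into the comparisons.* Only the fraction (1-r) does, and over randomisation the estimate is unbiased.
- *That a low-powered pre-test governs the analysis and distorts its error rate.* No formal test is named, the criterion is a detail that can be left to the SAP, and the simulations showed no inflation.
- *That a switch to ranks discards the mean difference and its interval.* The text replaces only the test. It still describes continuous variables by means, SDs and medians, and sets reported intervals at 95%.

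**Conclusion.** The point holds in two parts.

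The unadjusted change-score test is valid but gives up precision that the plan already takes for its primary outcome. ANCOVA would cut the variance by 35%, 25%, 15% and 5% at r = 0.3, 0.5, 0.7 and 0.9, and would remove the residual shift of -(1-r)d in expectation. These sizes assume equal variances at the two times and a linear relation between baseline and follow-up, with r chosen by me.

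The rank tests are in the wrong order as written. This does not depend on any assumption; it follows from reading the two sentences together.

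Neither part affects the primary analysis.

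**What to change.** - Analyse each continuous secondary outcome at 2 months (A to C versus D to F), and each immediate change (A to B versus D to E), by ANCOVA with that outcome's own baseline and age, as for the primary. Report the adjusted difference with its 95% confidence interval.
- Correct the fallback sentence so that Mann-Whitney replaces the two-sample t-test between groups and signed-rank replaces the paired t-test within a group, including F to G.
- Optional: fix in advance a log scale for the skewed urine and saliva markers, report ratios of geometric means, and keep the rank tests as sensitivity analyses.

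The cost is a few sentences of analysis wording. All baselines are already scheduled, and the article gives its status at submission as recruiting, so the change could be made before analysis.
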